| **Section 1: Clinical Research Definition** |
| --- |

**1.3 Clinical trial type**

| Clinical trial application without CE marking |  |
| --- | --- |
| Post-Market Surveillance (PMCF) application |  |
| Other clinical trial application |  |

**1.4 Application Type**

| First application in the European Economic Area (EEA) |  |
| --- | --- |
| First application at the national level (clinical trial already submitted in the EEA)  In this case, please enter the provided clinical trial identification number (CIV-ID). |  |
| Reapplication  In this case, please enter the CIV-ID if available. |  |

**1.5 Participating countries within the EU/EEA/United Kingdom (Northern Ireland), Turkey, and Switzerland**

| Turkey |
| --- |

**1.6 Participating countries outside the EU/EEA/United Kingdom**

| **Turkey** |
| --- |

**1.7 Clinical investigation plan (CIP)**

| CIP code: SEM-ART 1  CIP version: 1.0  CIP date: 10.07.2023 |
| --- |

**1.8 Clinical trial title**

| Full title: A Single-Center, DOUBLE-BLIND, PLACEBO-CONTROLLED CROSS-OVER RANDOMIZED POST-MARKET CLINICAL FOLLOW-UP (PMCF) STUDY  Short title: A POST-MARKET CLINICAL FOLLOW-UP STUDY EVALUATING THE EFFICACY AND SAFETY OF SEMİCAL GEL-B CROSS TREATMENT IN KNEE OSTEOARTHRITIS  Title for non-professionals:  The efficacy and safety of Semical Gel B Cross in knee osteoarthritis |
| --- |

| **Section 2: Clinical Study Description** |
| --- |

**2.1 Scientific opinion**

| Has the manufacturer consulted an expert committee as specified in Article 61(2) of the Medical Device Regulation?  Yes No |
| --- |

**2.2 Design of the Clinical Study**

| Basic clinical investigation Confirmatory investigation PMCF |
| --- |
| First study in humans Not the first study in humans |

**2.3 Design methodology**

| Case-control | | Controlled | Cross-sectional | Double-blind |
| --- | --- | --- | --- | --- |
| Parallel | | Randomized | Open |  |
| Other: |  | | | |

**2.4 Development phase**

| Phase 1 Phase 2 PMCF |
| --- |

**2.5 Objectives and Endpoints**

| Primary objective(s): |
| --- |
| Primary objectives: The objective of this study is to obtain short- and long-term clinical data on the performance and safety of SEMICAL GEL B-CROSS intra-articular gels manufactured and marketed by Semikal Technology Inc. |
| Secondary objective(s): |
| The study also aims to monitor known adverse events and complications, identify previously unknown adverse events and complications, and define and analyze emerging risks based on real-world data. |
| Other objective(s): |
|  |
| Primary endpoint(s): |
| - Change in pain due to knee osteoarthritis (will be assessed by change in WOMAC pain score at baseline, 3 months, 6 months, 9 months, and 12 months) |
| Secondary endpoint(s): |
| - Lower extremity functional score (using the WOMAC Function Index at baseline, 3 months, 6 months, 9 months, and 12 months) - Improvement in knee function (increase in muscle strength, 5 times sit-to-stand test, and walking distance; at Baseline, 3 Months, 6 Months, 9 Months, and 12 Months) - Decrease in analgesic treatment requirement (using pain diary) - Change in quality of life (using SF-36, at Baseline, 3 Months, 6 Months, 9 Months, and 12 Months) - Change in knee pain during movement and rest (using VAS, at Baseline, 3 Months, 6 Months, 9 Months, and 12 Months) - Local reactions at the injection site - Adverse events throughout the entire study period |
| Other endpoints: |
| Safety endpoints:  Evaluation of the tolerability and safety of the treatment by monitoring adverse events and complications   - Early adverse events and complications (number and severity of local reactions at the injection site; Day 0 – Day 10) - Late-phase adverse events and complications (Day 0 – 12 months) |

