**2.6 Summary of the clinical study**

| General summary:  The SEM-ART 1 study is a randomized controlled, double-blind, two-arm, single-center study. Following a maximum 28-day screening period, patients with Kellgren & Lawrence Stage II and III knee osteoarthritis will be randomly assigned to one of two treatment arms on the day of injection, considered Day 0. These treatment arms are:   1. Group: Treatment Arm – Cross-linked intra-articular hyaluronic acid (90 mg 3 ml cross-linked hyaluronic acid) 2. Group: Control Arm – Intra-articular isotonic saline solution (0.9% sodium chloride) at the same dose as the treatment arm   Study treatments will be administered once.  A safety visit will be conducted 7-10 days after the treatment injection, and the injection site will be visually assessed for local reactions. In addition, adverse events related to the injection will be investigated.  Patients will attend their first follow-up visit 3 months after the intra-articular injection. At this visit, the treatment responses of patients in both groups will be assessed by a separate evaluator who is blinded to the study treatment, using pre-specified objective response criteria.  Following this response evaluation at 3 months, the treatment received by patients in both groups will be switched, and they will receive the treatment administered to the other arm. That is, those receiving placebo will receive hyaluronic acid injection at 3 months, while those receiving hyaluronic acid injection will receive placebo at 3 months. Efficacy evaluations will continue at three-month intervals.  Performance evaluation will be demonstrated by the patients' treatment response and will be conducted at 3 months, 6 months, 9 months, and 12 months. In these evaluations:   - WOMAC osteoarthritis index - Assessment of pain levels over the past month using the Visual Analog Scale (two separate assessments will be taken for pain during activity and at rest). - Evaluation of the need for analgesic medication in the last month (using a patient diary) - Quality of life assessment (using the SF-36 questionnaire) - 6-minute walk test - 5 sit-to-stand tests - Assessment of muscle strength (using an isometric dynamometer/hand-held myometer)   Safety assessments will be performed throughout the study at each visit by monitoring adverse events and side effects, physical examination, and vital signs. In addition, serious adverse events will be closely monitored within the first 48 hours following intra-articular injections, and a safety follow-up visit will be conducted on days 7-10 after treatment to evaluate injection-related reactions. |

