| Is it registered in the Ministry of Health Product Tracking System (ÜTS)?  Yes No  If yes, please specify the global product number (barcode) for the product and attach the ÜTS output to the application file.  Global Product Number (Barcode): **8682190071187** | | | | |
| What is the intended use of the device within the scope of the clinical trial?  The CE-marked device will be used outside the scope of the CE marking.  The CE-marked device will be used within the scope of the CE marking.  The CE-marked device will be used within the scope of the CE marking, but additional procedures will be applied in the clinical trial. | | | | |
| Do these additional procedures involve any extra burden or invasiveness?  Yes No  If yes, please explain:  Patients included in this study will undergo the following procedures at three-month intervals at the beginning and throughout the study, which differs from routine clinical practice.   - Since the study is designed as a crossover trial, each patient will receive two intra-articular injections: one with hyaluronic acid and one with placebo. - 6-minute walk test - 5 sit-to-stand tests - Measurement of muscle strength using a myometer | | | | |
| If applicable, information regarding the relevant Notified Body:  Approved Body number: **2292**  Name of the Notified Body: **UDEM International Certification Inc.** | | | | |

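### The early safety window is tied to a Day 0 that means only the first injection, so as written it leaves out every month-3 crossover injection and sits wholly inside the late-phase window

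*Protocol*

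**What the plan says.** Section 2.5 gives two windowed safety endpoints: "Early adverse events and complications (number and severity of local reactions at the injection site; Day 0 – Day 10" and "Late-phase adverse events and complications (Day 0 – 12 months". It also lists, among the secondary endpoints, injection-site reactions with no time limit and adverse events over the whole study. The primary objective of this post-market study names safety alongside performance, and the secondary objective includes finding adverse events not known before.

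Section 2.6 fixes the clock: patients "will be randomly assigned to one of two treatment arms on the day of injection, considered Day 0". It then describes the crossover: "those receiving placebo will receive hyaluronic acid injection at 3 months, while those receiving hyaluronic acid injection will receive placebo at 3 months". Section 3.1.4 confirms that "each patient will receive two intra-articular injections: one with hyaluronic acid and one with placebo".

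Section 2.6 mentions the early safety visit twice. Ahead of the crossover paragraph it says: "A safety visit will be conducted 7-10 days after the treatment injection, and the injection site will be visually assessed for local reactions". In the closing safety paragraph it describes monitoring of serious events "within the first 48 hours following intra-articular injections, and a safety follow-up visit will be conducted on days 7-10 after treatment to evaluate injection-related reactions". Neither sentence says how many such visits a patient has.

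**The concern.** The protocol has one clock. Day 0 is the first injection, nothing resets it at month 3, and the visits at 3, 6, 9 and 12 months and the 12-month window all run on it. On that clock the early endpoint closes about 80 days before the second injection (taking 3 months as 90 days, 90 − 10 = 80). For patients who start on saline, the whole HA exposure comes after the early window has shut.

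Two things follow. First, the early count and severity grading of local reactions to HA rests on the HA-first group alone. An acute reaction to an HA injection at month 3 is the same kind of event, but among the windowed endpoints it can enter only the one labelled late-phase. Second, the late-phase window begins on the same Day 0, so the two labels do not separate early from late events: a reaction to the first injection meets both definitions, and one to the second meets only the late definition.

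At stake is the precision and clarity of the acute local-reaction profile of HA, in a study whose primary objective includes safety.

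**Working it through.** The protocol states no precision or rate for this endpoint, so there is no figure to reproduce. The check has three parts.

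**1. Windows against injections**

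| Injection | Product, HA-first | Product, saline-first | In Day 0–10? | In Day 0–12 months? |
| --- | --- | --- | --- | --- |
| Day 0 | HA | saline | yes | yes |
| Month 3 | saline | HA | no | yes |

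The early window lies entirely inside the late one.

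**2. HA injections outside the early window**

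Inputs: N = 102 (section 2.7); one HA injection per patient (section 3.1.4); allocation ratio not stated, so 1:1 is assumed and a range shown.

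Formula: HA injections at month 3 = N − (number randomised to HA first).

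- 1:1: 102 − 51 = 51, or 51/102 = 50%.
- 2:1 (HA first to saline first): 102 − 68 = 34, or 34/102 = 33%.
- 1:2: 102 − 34 = 68, or 68/102 = 67%.
- 1:1 with 10% of the saline-first group lost before month 3: 45.9/(51 + 45.9) = 47% of HA injections given.
- 1:1 with 20% lost: 40.8/(51 + 40.8) = 44%.

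**3. What this does to precision (illustration only)**

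The zero-event scenario and the true rates of 1% and 2% are assumptions chosen for illustration, with 1:1 allocation and no dropout.

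One-sided 95% upper limit on the reaction rate after zero events in n injections: 1 − 0.05^(1/n).

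- n = 51: 1 − 0.05^(1/51) = 5.7%.
- n = 102: 1 − 0.05^(1/102) = 2.9%.
- Across the allocation range, the HA injections inside the window as written are n = 68 (2:1) or n = 34 (1:2), giving 1 − 0.05^(1/68) = 4.3% and 1 − 0.05^(1/34) = 8.4%.

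Chance of seeing at least one reaction with true rate p: 1 − (1 − p)^n.

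- p = 1%: 1 − 0.99^51 = 40%; 1 − 0.99^102 = 64%.
- p = 2%: 1 − 0.98^51 = 64%; 1 − 0.98^102 = 87%.

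**The case against.** The strongest reply is that this is loose wording and that no safety data are missing. Much of it stands.

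- A reader might infer that reactions to the month-3 injections go unrecorded. The protocol does not support that. Section 2.5 also lists local reactions without a window and adverse events over the whole study, and the Day 0 to 12 months endpoint runs past month 3. The gap is confined to the early endpoint.
- A reader might infer that the day 7-10 visit follows the first injection only. That is not stated. The first mention, in the singular and ahead of the crossover, leans that way. The second ties 48-hour monitoring to injections in the plural and times the visit from treatment, which allows a visit after each. The text is open on this point, so it calls for reconciling and proves no omission. Even on the per-injection reading, however, the window in section 2.5 would still run from Day 0.
- A reader might infer that early events will be double counted, or that safety will be tabulated by randomised arm to month 12, when both arms have had both products. No section adds the two windows together or prescribes such a table. A Day 0 to 12 months window can be cumulative, and attribution by product may properly be in a statistical analysis plan that is not at hand.
- Section 2.6 is a summary, and the application refers to a separate clinical investigation plan that may give more visit detail.

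What the reply does not remove is that this document does fix the early window, and fixes it to a Day 0 that excludes half of the injections in a two-injection design.

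**Conclusion.** The concern holds as a defect of endpoint definition. Followed as written, the early local-reaction endpoint excludes all month-3 injections, including every HA injection in the saline-first group: 51 of 102 under 1:1 allocation and no dropout, 33% to 67% for allocations of 2:1 to 1:2, and 44% to 47% of HA injections given if 10% to 20% of the saline-first group is lost before month 3. Acute reactions to those injections are still captured elsewhere, but the only windowed endpoint that takes them is called late-phase and contains the whole early window.

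The improvement in the zero-event upper limit, from 5.7% to 2.9%, shows what the early endpoint would gain by covering all HA injections. It does not correct any claim in the protocol. It also applies only to the early endpoint, since a count of local reactions without a window would already include month 3. The finding rests on reading Day 0 in section 2.5 as section 2.6 defines it, the only definition the document gives.

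**What to change.** 1. In section 2.5, define the early window as day 0 to day 10 after each injection, and tabulate number and severity of local reactions by the product injected. With no dropout that gives 102 HA and 102 saline injections, one of each per patient.
2. Either start the late window after day 10 of each injection, or keep Day 0 to 12 months and label it cumulative so that it is not read as a separate phase.
3. For events after month 3, attribute with both exposures in view, for example by reporting the time since each injection. A contrast of HA with saline is cleanest before month 3 and within the 10-day windows.
4. Reconcile sections 2.5 and 2.6 on whether the day 7-10 safety visit applies after each injection.

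The cost is revised endpoint wording and minor table work. If step 4 shows that the visit was planned after the first injection only, the sponsor would have to settle how the early window after the second injection is to be assessed.

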**2.6 Summary of the clinical study**

| General summary:  The SEM-ART 1 study is a randomized controlled, double-blind, two-arm, single-center study. Following a maximum 28-day screening period, patients with Kellgren & Lawrence Stage II and III knee osteoarthritis will be randomly assigned to one of two treatment arms on the day of injection, considered Day 0. These treatment arms are:   1. Group: Treatment Arm – Cross-linked intra-articular hyaluronic acid (90 mg 3 ml cross-linked hyaluronic acid) 2. Group: Control Arm – Intra-articular isotonic saline solution (0.9% sodium chloride) at the same dose as the treatment arm   Study treatments will be administered once.  A safety visit will be conducted 7-10 days after the treatment injection, and the injection site will be visually assessed for local reactions. In addition, adverse events related to the injection will be investigated.  Patients will attend their first follow-up visit 3 months after the intra-articular injection. At this visit, the treatment responses of patients in both groups will be assessed by a separate evaluator who is blinded to the study treatment, using pre-specified objective response criteria.  Following this response evaluation at 3 months, the treatment received by patients in both groups will be switched, and they will receive the treatment administered to the other arm. That is, those receiving placebo will receive hyaluronic acid injection at 3 months, while those receiving hyaluronic acid injection will receive placebo at 3 months. Efficacy evaluations will continue at three-month intervals.  Performance evaluation will be demonstrated by the patients' treatment response and will be conducted at 3 months, 6 months, 9 months, and 12 months. In these evaluations:   - WOMAC osteoarthritis index - Assessment of pain levels over the past month using the Visual Analog Scale (two separate assessments will be taken for pain during activity and at rest). - Evaluation of the need for analgesic medication in the last month (using a patient diary) - Quality of life assessment (using the SF-36 questionnaire) - 6-minute walk test - 5 sit-to-stand tests - Assessment of muscle strength (using an isometric dynamometer/hand-held myometer)   Safety assessments will be performed throughout the study at each visit by monitoring adverse events and side effects, physical examination, and vital signs. In addition, serious adverse events will be closely monitored within the first 48 hours following intra-articular injections, and a safety follow-up visit will be conducted on days 7-10 after treatment to evaluate injection-related reactions. |
| --- |
|  |

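### The early safety endpoint counts and grades local reactions over Day 0 to Day 10, but no recording of non-serious reactions is described before a single visit at days 7-10

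*Protocol*

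**What the plan says.** Section 2.5 (Objectives and Endpoints) lists "Local reactions at the injection site" as a secondary endpoint. Under the safety endpoints it defines the early component as "number and severity of local reactions at the injection site; Day 0 – Day 10". The primary objective in the same section covers short- and long-term safety as well as performance, and the secondary objective includes finding adverse events not known before.

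Section 2.6 (Summary of the clinical study) describes how early safety is followed:

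- One early visit: "A safety visit will be conducted 7-10 days after the treatment injection, and the injection site will be visually assessed for local reactions".
- An enquiry at that visit: "In addition, adverse events related to the injection will be investigated".
- Closer attention at the start: "serious adverse events will be closely monitored within the first 48 hours following intra-articular injections".
- A general provision: "Safety assessments will be performed throughout the study at each visit by monitoring adverse events and side effects, physical examination, and vital signs".

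Sections 2.5 and 2.6 name a diary only for pain and for the need for analgesics. Section 2.6 ties the analgesic item to the preceding month and to the evaluations at 3, 6, 9 and 12 months.

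**The concern.** A count with severity over a window needs observation or recording across that window. Here the endpoint starts at the injection, but the one scheduled look at the site for local reactions comes 7 to 10 days later. Ordinary redness, swelling or pain at the site is not normally a serious adverse event, so the 48-hour monitoring as worded does not call for recording it.

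What is at stake is a named safety endpoint of a post-market study. If short-lived reactions enter only through recall, the reported rate is likely to be too low and the grades uncertain. A statistical analysis plan cannot repair this, because it cannot supply observations that were not made. The primary WOMAC pain endpoint is not affected. The point is about when reactions are recorded, not about which injection the window is counted from.

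**Working it through.** The protocol gives no reaction rate, duration or detection figure, so there is no trial figure to reproduce. The check sets the endpoint window against the schedule.

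**Coverage of the window (sections 2.5 and 2.6)**

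| Part of the window | What is described | Are non-serious local reactions recorded? |
| --- | --- | --- |
| Day 0 | Injection visit; general adverse event monitoring and physical examination apply to every visit | Only what appears before the patient leaves |
| First 48 hours | Close monitoring of serious adverse events | Not named |
| After 48 hours until the visit | No visit, contact or reaction diary | No |
| Day of the visit (7, 8, 9 or 10) | Visual inspection, and enquiry into injection-related adverse events | Yes: what is present is seen, what has resolved is recalled |
| After the visit until day 10 | Nothing before the 3-month visit | No |

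The last row depends on the visit day. A visit on day 7 leaves 10 − 7 = 3 days (8, 9 and 10) uncovered; a visit on day 10 leaves none.

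**What inspection alone would see (illustration on assumptions)**

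Assume onset on Day 0 and an exponential duration with mean m days. The share still visible on day t is exp(−t/m).

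| Assumed mean m | Day 7 | Day 10 |
| --- | --- | --- |
| 1 day | exp(−7) = 0.1% | exp(−10) = under 0.01% |
| 2 days | exp(−3.5) = 3.0% | exp(−5) = 0.7% |
| 3 days | exp(−2.33) = 9.7% | exp(−3.33) = 3.6% |
| 5 days | exp(−1.4) = 24.7% | exp(−2) = 13.5% |

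These are shares visible at inspection, not shares captured by the trial. Recall adds to them by an amount that the document does not allow one to estimate.

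**Effect on the comparison with saline**

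Let the true reaction rates be p1 (hyaluronic acid) and p0 (saline), and let c1 and c0 be the shares captured.

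- Equal capture, c1 = c0 = c: the observed difference is c(p1 − p0), smaller than the true one, while the ratio p1/p0 is unchanged.
- Unequal capture: the observed ratio is (c1/c0)(p1/p0). Suppose hyaluronic acid reactions lasted 5 days on average and saline reactions 2 days. Inspection alone on day 7 would then give c1/c0 = 24.7/3.0 = 8.2, so equal true rates would look very different.

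The direction of the bias in the comparison is therefore not fixed by the document.

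**The case against.** The strongest reply is that nothing here is a flat contradiction. A visit at days 7-10 can ascertain events since the injection by history, and section 2.6 says that injection-related adverse events will be investigated there. Adverse events are also monitored at every visit, and the 48-hour sentence adds attention to serious events without saying that others are ignored. Day 0 is itself a visit.

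This stands, and it limits the point. A reader might infer that short-lived reactions are missed altogether, or that the visual inspection is the only assessment of them. The text does not support either reading, because retrospective enquiry is planned. Nor may the illustrative percentages be read as the share lost: the durations are assumed and recall is left out. A claim that late inspection must shrink the difference between the arms also fails, since it needs equal capture in both arms and even then applies to the absolute difference only.

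A second reply is that this is a summary within an application form. The clinical investigation plan and case report form are separate documents (sections 1.7 and 6.1) and may hold diary items and grading scales. That is fair, and the absence of a grading scale is not held against the text. But section 2.6 does set out the early safety procedures, and as set out they do not cover the window that section 2.5 defines.

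**Conclusion.** The point holds in a limited form. As written, non-serious local reactions that resolve before the day 7-10 visit are not directly observed. They can be reported at that visit, but are likely to be under-counted and graded from memory. With a visit on day 7, days 8-10 are uncovered.

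The size of the loss cannot be derived from the document. On the assumed mean durations of 1 to 5 days, inspection alone would find at most about a quarter of Day 0 reactions still visible on day 7; what recall recovers is unknown. The effect on the hyaluronic acid versus saline comparison depends on whether capture and reaction duration are equal in both arms. This is a cheap improvement to a named safety endpoint, not a flaw in the primary efficacy comparison. The conclusion assumes that no prospective recording is set out in a document not shown here.

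**What to change.** In section 2.6:

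1. Have patients record injection-site pain, redness and swelling, each with a grade, daily for days 0-10 after each injection. Add lines to the patient diary for this and state that the diary covers those days, since the present text does not show that it does.
2. Include local reactions in the 48-hour monitoring.
3. Use the day 7-10 visit to review the entries to date. Entries after an earlier visit complete the window.

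If prospective recording is not wanted, redefine the endpoint in section 2.5 as local reactions present or recalled at the day 7-10 visit, so that it matches what is measured.

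The cost is a few diary lines, a small added burden for patients and probably a higher reported reaction rate. The change itself calls for no extra visit. Whether the 48-hour monitoring already involves a contact that could carry the question is not stated and should be made clear.
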